## Abstract

**Background:**

Prevention of childhood obesity is a key approach to the primary prevention of noncommunicable diseases. Several models, based on the population health approach and aligned with ecological models, are used to design childhood obesity prevention programs around the world.

**Objective:**

This study aims to introduce the design and evaluation plan of “Iran Healthy Start (IHS)/Aghazi Salem, Koodake Irani”—the customized Iranian version of Canadian Healthy Start/Départ Santé health promotion program—which is now being developed in Mashhad University of Medical Sciences (Mashhad, Iran) and focuses on improving physical activity and healthy eating among preschool children.

**Methods:**

We will evaluate the intervention using a pilot randomized controlled design. The components of intervention include customized Decoda Web-based resources for children, an implementation guide for educators and managers, training and monitoring, communication and knowledge exchange, building partnership, and parent engagement. Outcomes include changes in anthropometry, physical activity level, nutritional risk status and dietary intake, and quality of life.

**Results:**

The project is funded by Mashhad University of Medical Sciences. The intervention was completed by the end of March 2018, and the analysis is currently under way. The first results of the IHS intervention program are expected to be submitted for publication in December 2018.

**Conclusions:**

The double burden of malnutrition in early years children is a major health concern in developing countries. This justifies the need for health promotion programs that are specifically designed to target both overnutrition and undernutrition prevention. If the efficacy approved, the IHS could potentially be a comprehensive health promotion program for young children whose lifestyle behaviors can be improved toward a healthy future life in a nutrition transition setting.

**Trial Registration:**

International Clinical Trials Registry Platform IRCT2016041927475N1; https://en.irct.ir/trial/22497

**International Registered Report Identifier (IRRID):**

RR1-10.2196/11329

## Introduction

At present, noncommunicable diseases (NCDs) and obesity—as the main predisposing factor of NCDs—are the most common cause of mortality and morbidity, with a higher prevalence in low-income and middle-income countries [1]. The World Health Organization (WHO) has introduced NCDs as the major challenge for development and emphasizes the need for urgent action to prevent and control NCDs [2]. Among the NCDs’ risk factors, obesity needs particular attention, as metabolic syndrome and diabetes are directly associated with obesity [3,4]. Early childhood obesity is associated with a higher risk of developing NCDs at a younger age and premature death in adulthood [5,6], as adiposity tracks into adulthood [7]. Prevention of childhood obesity is a key approach to the primary prevention of NCDs [3]. Based on the WHO report, in 2016, an estimated 42 million children aged <5 years are overweight or obese, while around 70% of them live in Asia and Africa [8]. In Iran, according to the latest report of an Iranian national survey on May 2015, which was conducted in 30 provinces, the prevalence of overweight, obesity, and abdominal obesity among children and adolescents aged 6-18 years was 9.7%, 11.9%, and 19.1%, respectively [9].

After the announcement of the WHO on February 2015, regarding the urgency of ending childhood obesity around the world, societies and governments took urgent and meaningful action to address this issue. Childhood obesity is a complex and multidimensional health problem, and usually, single and narrow target interventions do not succeed. Evidence suggests that improving healthy eating and physical activity behaviors are the cornerstone for weight management strategies [10,11], along with decreasing sedentary activities [12,13] and maintaining healthy sleep patterns [14,15], Most recent intervention strategies have focused on modifying environment in a way that provides healthy options for children and increases opportunities for physical activity and healthy eating.

In developing countries, such as Iran, nutrition transition is occurring side-by-side with epidemiological transition. A history of low birth weight or stunting, which still exists in developing countries, is a risk factor for later overweight and obesity in children and consequent cardiovascular diseases or diabetes [16]. According to the data released from the WHO, United Nations International Children’s Emergency Fund, and World Bank Group in 2016, Middle East and North Africa, which mainly include higher middle-income countries, have the highest prevalence of overweight and obesity (10.7%) after Eastern Europe and Central Asia (12.8%) among global regions, while the prevalence of coexisting stunting is 15.3% among Middle Eastern and North African countries [17]. The presence of both overweight and underweight in a population or even in families is recognized as “double burden of malnutrition” and highlights the importance of nutrition in early life and its close relation with later-life health conditions [8]. In such a situation, the question arises, “How can an obesity prevention program be conducted, where the problem of overweight and underweight simultaneously exists among children?”

Several childhood obesity prevention programs using different models based on the population health approach [18,19], and aligned with ecological models [20], have been designed and conducted around the world with different scientific rationale [21,22]. Interventions that adhere to principles of the population health approach are designed in accordance with the fact that in a comprehensive population health approach, all levels of impact, such as the intrapersonal (psychological and biological), interpersonal (psychological and social), institutional, community (resources and facilities), and governmental policy, should be included and stimulated to promote the achievements. Healthy Start/Départ Santé (HSDS) is a health promotion program, designed as a population health intervention aiming at promoting physical activity and healthy eating among both Anglophone and Francophone preschoolers in early daycare or preschools in Canada. HSDS is composed of the following 6 interlinked components: (1) evidence-based resource, “Literacy, Education, Activity, Play (LEAP)” from the Decoda literacy Web-based resources [23,24]; (2) HSDS implementation guide; (3) training and monitoring; (4) intersectoral partnership; (5) additional resources; and (6) communication, knowledge development, and exchange. In the evaluation of the HSDS intervention program, 230 children aged 2.5-4 years from very diverse sociocultural and economic backgrounds, from 10 childcare centers, were involved in the project. The results clearly represented groundbreaking and innovative work. Improvements were seen in healthy eating children, physical activity, and childcare environment. Healthy Start has been developed and initiated in the Saskatchewan province of Canada and is expected to expand to the whole country and other countries around the world. The first report of HSDS was released on November 2012 [25].

To address the challenge of childhood obesity and the double burden of malnutrition in a developing country, we decided to calibrate and customize HSDS as a health promotion initiative, which is now successfully running in 2 provinces in Canada [26]. “Iran Healthy Start (IHS)/Aghazi Salem, Koodake Irani” is the customized Iranian version of Canadian HSDS health promotion program, which is now being developed in Mashhad University of Medical Sciences (MUMS; Mashhad, Iran) and focuses on improving physical activity and healthy eating among preschool children. The principles of IHS are adapted from the original Canadian HSDS, considering unique conditions that exist in the Iranian culture, preschool education bylaws, curriculum, and environment.

Study objectives.To customize and implement the health promotion program (Iran Healthy Start), aligned with preschool bylaws in IranTo determine whether Iran Healthy Start program can:Increase physical activity level and attraction to physical activity among preschoolersReduce sedentary behaviors at home among preschoolersImprove anthropometric parameters in preschoolers toward healthy weightsImprove quality of life in preschoolersImprove eating habits and nutrition risk among preschoolersTo evaluate the feasibility, attrition rate, as well as facilitators and barriers for implementing this program in Iranian preschoolsTo calibrate measurement tools: validating the Persian translation of Nutrition Screening Tool for Every Preschooler and Children Attraction toward Physical Activity

From our point of view, some characteristics of HSDS make it more relevant to what we need. The key characteristic of HSDS is that it is based on evidence-based ecological framework [27] and adheres to the population health approach. Furthermore, it introduces strategies for all levels of influence. Another advantage of this program is its multicultural nature, which makes the program more relevant at the international stage and makes the customization easier, although it requires fundamental modifications to be feasible for Iranian preschool children. HSDS targets all children, regardless of their weight or risk of obesity, which is the primary prevention initiative (health promotion) in the public health approach. This level of prevention includes fundamental activities that are directed at reducing the risk of exposure to a risk factor in an individual or the population [28].

Textbox 1 shows the objectives of this study.

## Methods

### Study Description

This section is addressed on the basis of the Standard Protocol Items: Recommendations for Interventional Trials [29]. In a multisectoral approach, the key stakeholders, including Departments of Nutrition, Chancellor for Health and Chancellor for Research in MUMS, Provincial Education Department, and Nutrition Affairs Department of the Iranian Ministry of Health and Medical Education, are involved in the “IHS” program. The IHS is supported and funded by MUMS. A memorandum of understanding was signed between MUMS and HSDS lead organization (Saskatchewan Network for Health Services in French—Réseau de Santé en Français de la Saskatchewan) in Canada.

### Providing the Intervention Material

Prior to the evaluation, we need to provide the material and equipment for children and educators, as well as materials for engaging parents. This step requires the active involvement of the expert panel for the development and customization of the educational content and assistants for providing the toolkit and supplementary materials for implementation.

#### Development of the Intervention Components, Materials, and Customization Process

Considering some basic differences between Iranian and Canadian education environment and principles, the following criteria were determined for the development and customization of the intervention components and content: (1) Iranian preschool education bylaws; (2) current nutrition and physical activity guidelines for preschoolers; (3) physical area or environment in most preschools in Iran; (4) Iranian common plays, lyrics or songs, and play tools among preschool children; (5) Iranian culture (menu, common foods, and eating culture); (6) known foods preferred by Iranian children of this age; and (7) commonly available foods and their cost. For this purpose, an expert panel, including a nutritionist, physical activity expert, epidemiologist, representative of Provincial Education Department, graphist, psychologist, and an expert in children plays and lyrics, gathered in eight, 2-hour meetings to reach a consensus. Accepted modifications for each component or material or activity unit were registered by the secretary.

#### The Intervention

The IHS program has 6 components (Table 1):

*Customized LEAP*: Comprises two illustrated handbooks.Physical activity: containing 20 activity units along with a complementary chapter containing information for educators (ISBN: 2-25-7457-600-978).Nutrition: containing 20 activity units along with a complementary chapter containing information for educators (ISBN: 9-26-7457-600-978).The activity units were translated and customized on the basis of the criteria discussed during the “customization” process. This handbook is accompanied with “Healthy-kid Toolkit,” which contains utilities and materials for LEAP activity units.*IHS Implementation Guide*: A handbook for managers and educators containing modified self-assessment tool, as well as principles of the program, action planning, policies and practices, details of implementation, log pages, and report pages for both educators and managers. It also contains a suggested healthy weekly menu for serving a snack or a hot meal for children at preschool.*Training and Monitoring*: Comprises on-site training workshop followed by a supplementary booster session during the implementation (3-4 hours), as well as ongoing support through mobile and internet-based contacts (telegram) and weekly visits. The initial workshop introduces the program, objectives, customized LEAP activity units, IHS Toolkit, and resources. Educators and managers of intervention centers are invited to become a member of the IHS telegram channel, which is the most popular internet-based social network among Iranians. The implementation is monitored by weekly visits and daily logs and checking videos and photos while children do the activities every day.*Building Partnership*: Attracting the participation of key stakeholders and policy makers:Ministry of Health and Medical Education: Nutrition Affairs Department of the Ministry was informed about the details of the project from the inception of the project. The results of this pilot study will be reported to the aforementioned department for further steps toward the national implementation of the program.Provincial broadcasting (radio and television): A television show and radio talks related to childhood obesity, physical activity in children, healthy nutrition, parenting, and many other related topics were recorded to introduce the program and report the future outcomes.Provincial Education Department: Aiming at incorporating this program or any of its components into the current preschool education bylaws, several meetings were arranged with heads-in-charge.*Parent Engagement*: This is the main distinction between HSDS and IHS and includes the following:A scientific, user-friendly, and simple book entitled, “Knowledgeable Parents, Healthier Children,” for parents aiming at improving their knowledge and practice regarding healthy eating for the whole family, especially their preschool child (ISBN: 5-24-7457-600-978).Routine monthly meetings between parents and IHS team nutritionists.A 107-page book, which is written for parents, contains 5 main chapters as follows: (1) childhood obesity, the epidemic health problem; (2) the importance of healthy nutrition and physical activity for children; (3) the role of parents in children weight management; (4) parental challenges and worriment; and (5) specific nutrition and activity considerations for a preschool child. Parents are asked to read each chapter during one month. In monthly meetings, the content of each chapter is again explained and discussed for parents. These parent-nutritionist meetings are mutual, and parents are allowed to ask questions or share their comments or experiences regarding children’s nutrition and activity issues. This book is written by 2 team members ([name]). Before releasing this resource, 3 collaborating mothers were selected to read the book and share their comments regarding the fluency, practicality, and usefulness of content, as well as suggestions for adding topics or other required data.*Communication and Knowledge Exchange*: The purpose of this component is maintained by a comprehensive website [30] containing details of the program, pages for managers, educators, parents, and children, as well as social media tools and reports of the study findings for the stakeholders. This component is expected to improve knowledge, engagement, motivation, and level of cooperation in stakeholders, as well as knowledge translation and dissemination of the program and findings.

Tables 1 and 2 show a brief introduction of components of the Canadian HSDS and IHS programs. The Canadian HSDS program [26] consisted of children aged 2-5 years, and the duration of intervention was 11 months. The Iranian IHS program consisted of children aged 4-6 years, and the duration of intervention was 6 months.

**Table 1 table1:** Brief introduction of the components of the Healthy Start/Départ Santé program.

Program components	Implementation items
Literacy, Education, Activity, Play	Illustrated handbook containing healthy opportunities for preschoolers and Food Flair
Healthy Start/Départ Santé Implementation Guide	Handbook for directors and educators
Training and monitoring	On-site training session, which includes the monitoring of Healthy Start/Départ Santé in the center, as well as a supplementary training session (1-2 hours)
Partnership	Partnerships and linkages with key stakeholders, decision, and policy makers
Additional resources	Supplementary resources from the government
Communication, knowledge development, and exchange	Hands-on material, website, social media tools, dissemination of evaluation findings, and communications through mainstream media releases

**Table 2 table2:** Brief introduction of the components of the Iran Healthy Start program.

Program components	Implementation items
Customized Literacy, Education, Activity, Play	Illustrated handbook containing customized Literacy, Education, Activity, Play based on the Iranian preschool education bylaws, current nutrition, and physical activity guidelines for preschoolers, physical area, or environment in most preschools in Iran, Iranian common plays and lyrics or songs among preschool children, Iranian common playing tools and materials, Iranian culture (menu, common foods, and eating culture), known foods preferred by Iranian children of this age, and commonly available foods and their cost.
Iran Healthy Start implementation guide	Translated handbook for directors and educators
Training and monitoring	On-site training workshop and a supplementary booster session. The implementation is monitored by weekly visits and daily logs and sending videos and photos while children do the activities
Building partnership	Attracting the participation of the following: Ministry of Health by reporting results of the pilot study and proposing the national governmental program Iran broadcasting (radio and television) to introduce the program and report the outcomes Provincial Education Department for incorporating the designed material into the preschool education bylaws
Parent engagement	A 107-page book provided for parents, containing 5 main chapters to be discussed in each gathering session of parents and IHS team nutritionist (routinely every month)
Communication and knowledge exchange	Website, social media tools, and reports of the study findings for the stakeholders

### Development of the Evaluation Plan and Designing the Pilot Study

#### Obtaining Required Approval and Licenses

Conducting any educational interventions in preschools and schools in Iran needs a valid license from the Provincial Education Department. This license was obtained on October 8, 2016. MUMS and Chancellor for research provided the financial support. The study is approved by the Ethics Committee of MUMS (code: IR.MUMS.fm.REC.1395.208; September 25, 2016) and registered in Iranian Registry for Clinical Trials (ID: IRCT2016041927475N1; November 12, 2016) and is accessible through the WHO database of clinical trial registries. A comprehensive memorandum of understanding was entered between Chancellor for Health, MUMS and Saskatchewan Network for Health Services in French—Réseau de Santé en Français de la Saskatchewan (April 2017).

#### Development of the Evaluation Plan

##### Study Design

The evaluation of the IHS program is designed as a pilot randomized controlled trial. For recruitment, officially registered preschools in the Provincial Education Department database are stratified according to the socioeconomic status of people living in that area. The three levels of high, middle, and low socioeconomic areas are defined according to the categorization of the Provincial Education Department. Two preschools are randomly selected from each socioeconomic level (a total of 6 centers) and then allocated to the intervention and control groups (Figure 1). Overall, 3 centers in the intervention group (each center belongs to a different socioeconomic level) and 3 centers in the control group are defined. The selected centers are contacted in person and provided with comprehensive information. After confirmation of managers, 2 classes are randomly selected for enrollment (6 classes in the intervention group and 6 classes in the control group). Then, the parents of eligible children are invited in a meeting in preschool, and informed consent is obtained after a brief introduction on the whole program and the role of parents (for parents of the intervention group) and informing parents for data collection and cooperation in filling questionnaires (for parents of the control group). The components of the intervention program for managers, educators, children, and parents are conducted in intervention classes, and control classes receive the conventional preschool education program. Aiming to acknowledge the cooperation of control preschools, the wait-list approach is suggested to the managers to receive the intervention in the next educational year, as well as a comprehensive report for growth, nutrition, and physical activity status of each child, which is given after the intervention, is completed.

The intervention lasts for 6 months. The duration of an educational year in preschools in Iran is the same as elementary schools and lasts for 8 months (October-May). From March 21, there are around 2-week New Year (Norouz) holidays. The intervention will be completed before Norouz holidays. The required data are collected at baseline and after the completion of the intervention period.

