##### Participants and Data Collection

In the Iranian preschool bylaws, preschool is not a mandatory level, and all children aged 4-6 years can be registered either in preschool-1 (age, 4-5 years) or preschool-2 (age, 5-6 years). All children aged 4-6 years of the selected classes of each center are included in the study after a valid consent from their parents or legal guardian, while those with known chronic disease, such as cardiovascular, respiratory, endocrine, or musculoskeletal problems—after physician inquiry—as well as those who need to adhere to a specific diet, such as gluten-free or phenylalanine-free diets, are excluded.

Data reflecting the nutrition status, diet quality, physical activity and sedentary behaviors, quality of life, and anthropometry of children, as well as the general sociodemographic status of participants and their families are collected at baseline and after the intervention is completed (Table 3). Data collection is performed by a team of 4 nutritionists who are given comprehensive training to standardize the data collection. They learned how to consistently obtain anthropometric measurements, fill the required questionnaires, and train the use of pedometers and filling the parent-report questionnaires to parents. Data entry is done by one person for consistency (a PhD student). Each preschool takes about 7-10 days to collect all the required data. As parents’ cooperation is very important in the data collection, aiming to acknowledge their cooperation, especially in control preschools, a gift for children and a free nutrition consultation for children and their parents, as well as a comprehensive report for child growth, nutrition, and activity status, are dedicated.

As this is a pilot study and we cannot estimate the attrition rate, there is no need to define the sample size, but sample characteristics represent the population of preschool children in Mashhad.

**Table 3 table3:** Overview of the study process.

Group and action		Months	

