##### Data Analysis

Descriptive analysis (frequency, percentage, mean, and SD) will be used to characterize and compare the basic characteristics of participants in the intervention and control groups. Outcomes related to nutrition and physical activity will be compared between the intervention and control groups to seek any possible improvements following the intervention. Considering the number of intervention (n=152) and control (n=148) participants, which anticipates a normal distribution, independent sample *t* test, and chi-square tests will be used for between-group comparisons, while paired sample *t* test and MacNemar tests will be used for analyzing within-group changes. Any possible covariates will be controlled with the analysis of covariance test. All tests are 2-tailed, and a significance level of <.05 will be considered statistically significant. Data analysis will be done by IBM SPSS Statistics for Windows, version 23.0 (IBM Corp).

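### The class draw is not stratified by preschool level, so with only 12 classes sampled the arms may differ in age by chance, and no age adjustment is fixed

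*Protocol article*

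**What the plan says.** Study Design sets out the sampling chain. Registered preschools are "stratified according to the socioeconomic status of people living in that area". Next, "Two preschools are randomly selected from each socioeconomic level (a total of 6 centers"), and these are allocated so that each arm has one centre from each socioeconomic level. Finally, once the managers have agreed, "2 classes are randomly selected for enrollment", giving six classes in each arm.

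Participants and Data Collection describes the classes: children "can be registered either in preschool-1 (age, 4-5 years) or preschool-2 (age, 5-6 years"). It adds that "All children aged 4-6 years of the selected classes of each center are included in the study", subject to consent and the medical and dietary exclusions.

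Data Analysis gives 152 intervention and 148 control children. It uses independent-sample t tests and chi-square tests between groups, with a general promise of analysis of covariance for covariates. Neither age nor preschool level is named there.

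**The concern.** Level fixes a child's age to within a year, and whole classes enter the study. Age is therefore sampled mainly through 12 classes, not through 300 separate children. The rule as written permits two preschool-1 classes in one centre and two preschool-2 classes in the other centre of the same socioeconomic pair.

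Several outcomes plausibly depend on age over this range and are not described as age-standardised: weight, height, waist and arm circumference, pedometer steps, the activity-attraction score, dietary intake and quality of life. The quality-of-life form is the version for ages 5-7 (Quality of Life section), so its fit also varies with level. If the arms differ in level, part of an unadjusted difference between them reflects age and not the programme.

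**Working it through.** The plan states no figure for age balance, so there is none to reproduce.

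**Inputs from the article.** Three centres per arm and two classes per centre (Study Design); age bands 4-5 and 5-6 years (Participants and Data Collection); 152 and 148 children (Data Analysis). Mean class size is (152 + 148)/12 = 25, in line with the 20-30 per class given in the Discussion.

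**Assumptions.** Level mean ages of 4.5 and 5.5 years (band midpoints), equal class sizes, and the same level mix in every centre. The article does not state the mix, so it is varied.

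**Step 1: age gap per class.** Let d be the difference between arms in the number of preschool-2 classes. Each class is one sixth of an arm and the levels are 12 months apart, so the mean age gap is 12d/6 = 2d months. A gap of 4 months is |d| = 2, and 6 months is |d| = 3.

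**Step 2: many classes per centre, half at each level.** Then d is distributed as Bin(12, 1/2) - 6.
- P(|d| ≥ 2) = 1 - (792 + 924 + 792)/4096 = 1 - 2508/4096 = 0.388
- P(|d| ≥ 3) = 1 - (2508 + 2 × 495)/4096 = 1 - 3498/4096 = 0.146
- SD of the gap = 2 × √(12 × 1/4) = 3.46 months

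**Step 3: two classes of each level per centre.** The number of preschool-2 classes drawn is 0, 1 or 2 with probability 1/6, 4/6, 1/6, and d is the sum of six independent terms taking -1, 0 or 1 with those probabilities.
- P(d = 0) = 13236/46656 = 0.284
- P(|d| = 1) = 2 × 10224/46656 = 0.438
- P(|d| ≥ 2) = 1 - 0.284 - 0.438 = 0.278, and P(|d| ≥ 3) = 0.072
- SD of the gap = 2 × √(6 × 1/3) = 2.83 months

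**Step 4: other mixes, by the same calculation.**

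| Class mix in each centre | P(gap ≥ 4 months) | P(gap ≥ 6 months) |
|---|---|---|
| Many classes, 50:50 | 0.39 | 0.15 |
| Many classes, 70:30 | 0.34 | 0.11 |
| Many classes, 80:20 | 0.27 | 0.07 |
| Many classes, 90:10 | 0.13 | 0.02 |
| 3 + 3 classes | 0.33 | 0.10 |
| 2 + 2 classes | 0.28 | 0.07 |
| 1 + 3 classes | 0.22 | 0.03 |
| 1 + 2 classes | 0.19 | 0.02 |
| 1 + 1, or all one level | 0 | 0 |

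**Step 5: benchmarks, with ages uniform within bands.** Individual randomisation over ages 4-6 would give an SD of 24/√12 = 6.93 months and a standard error of the age difference of 6.93 × √(1/152 + 1/148) = 0.80 month. A draw balanced on level leaves only within-level age: SD 12/√12 = 3.46 months and standard error 3.46 × √(1/152 + 1/148) = 0.40 month. Against these, the unstratified draw has an SD of 2.83 to 3.46 months in Steps 2 and 3.

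**The case against.** The strongest reply is that this argues from brevity. The article gives the class draw part of a sentence, the flow diagram is not shown, and the full protocol might say that the draw was made within level. Nothing in the article contradicts itself on this point. That caution stands: the text does not establish that level was deliberately ignored. It does name socioeconomic area as the only stratifier, and it describes a plain random draw.

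The size also rests on an unknown mix. The Discussion describes cramped premises, which does not suggest many parallel classes. If each centre had one class per level, the problem disappears. In every mix tabulated, a gap of 4 months or more is less likely than not.

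The design has further protection. Outcomes are measured at baseline and at the end, and the Abstract frames them as changes, so a stable age difference largely cancels. BMI percentile and BMI z-score are already standardised for age. The covariance sentence in Data Analysis could cover age, and naming covariates can be left to an analysis plan. All this reduces the consequence. It does not remove it: the between-group tests named are unadjusted, the covariance sentence commits to neither age nor the baseline value, and six-month change may itself depend on age.

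A reader might also infer that level imbalance confounds the arms with a different curriculum. The article does not support this: the Discussion describes the mandatory teaching books for preschool children in general, not by level.

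**Conclusion.** The point holds as an avoidable risk of chance imbalance. Under the stated assumptions, the probability of a mean age gap of at least 4 months is about 0.13 to 0.39 over plausible mixes, and 0 in the two special cases. The range assumes the same mix in every centre; mixes that vary between centres are not covered by it.

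A reader might go further and infer that the arms probably do differ in age, or that the design is biased toward one arm. Neither follows. The realised classes are not reported, and a random draw favours neither arm. No bias in any particular outcome can be computed, because the article gives no relation between age and outcome. The consequence is mainly for outcomes that are not age-standardised, after the baseline measurements have removed part of it.

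**What to change.** **For this trial.** The Results section says the intervention is complete, so the draw cannot be changed. Report preschool level and age by arm. In Data Analysis, replace the unadjusted t test by an ANCOVA with child age (or preschool level) and the baseline value of the outcome as covariates fixed in advance. Both are obtainable from data the study already holds, so the cost is a sentence and a slightly larger model. This deals with age only; allowance for clustering by centre and class is a separate matter.

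**For a successor trial.** Replace the class-draw sentence with a rule such as: *In each centre, one preschool-1 class and one preschool-2 class are drawn at random. Where this is not possible, both centres of a socioeconomic pair contribute the same level mix, and pairs are chosen so that they can.* This makes the level difference between arms exactly zero with the same number of classes. The small downside is the fallback for centres without both levels, which narrows the choice of pairs.
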